## **Generalisability**

Variables are defined in such a way as to help the generalisability of the model to other settings (see table below). For instance, deprivation will be included in the model in deciles rather than as a continuous variable in order that other deprivation measures that are used in other settings can be included in the same model to obtain predicted probabilities. When the final model is used for prediction, it is possible that some variables that are included as covariates may be missing. We will provide guidelines for using the model for prediction in this scenario, for example by using mean imputation of the missing variable.

## Appendix 1: List of risk factor variables

Time varying covariates (e.g. age) are used based on the value at diagnosis. Variables referring to 'previous' events are based on events that happen on or before the date of diagnosis. 'Group' (see section 'Adjustment for risk factors' in main document) refers to the model for violent crime; group allocation for the suicide outcome is given in brackets, where this is different. A dash (-) indicates a variable that will not be included in the model.

| Variable                       | Group | Type        | Notes                                                                                                                                                                                                                                                                                         |
|--------------------------------|-------|-------------|-----------------------------------------------------------------------------------------------------------------------------------------------------------------------------------------------------------------------------------------------------------------------------------------------|
| Sex                            | 1     | Binary      | Male / female                                                                                                                                                                                                                                                                                 |
| Age                            | 1     | Continuous  |                                                                                                                                                                                                                                                                                               |
| Previous violent crime         | 1     | Binary      | Any violent crime conviction before date of diagnosis.                                                                                                                                                                                                                                        |
| Previous drug use              | 1     | Binary      | Use disorder or dependence                                                                                                                                                                                                                                                                    |
| Previous alcohol use           | 1     | Binary      | Use disorder or dependence                                                                                                                                                                                                                                                                    |
| Previous self-harm             | 1     | Binary      |                                                                                                                                                                                                                                                                                               |
| Educational level              | 1     | Categorical | Seven categories, ranging from less than 9 years primary and lower secondary education (level 1) to postgraduate education (level 7); converted to three categories for analysis (primary/lower secondary education (1/2), upper secondary education (3/4), post-secondary education (5/6/7)) |
| 'Immigrant descent'            | 1     | Binary      | Either individual born abroad, or either parent born abroad                                                                                                                                                                                                                                   |
| Parental drug or alcohol use   | 1     | Binary      | Parental previous drug use and parental previous alcohol use will be combined into a single variable                                                                                                                                                                                          |
| Parental violent crime         | 1 (3) | Binary      |                                                                                                                                                                                                                                                                                               |
| Sibling violent crime          | 1 (3) | Binary      |                                                                                                                                                                                                                                                                                               |
| Diagnosis                      | 2     | Binary      | Classified as either 'bipolar' or 'schizophrenia' (the latter also covers the schizophrenic spectrum)                                                                                                                                                                                         |
| Recent treatment – drug class  | 2     | Categorical | Four categories (each treated as binary: 'mood', 'antipsychotic', 'antidepressant', 'dependence'); defined as any prescription collected in the six months prior to diagnosis                                                                                                                 |
| In/outpatient diagnosis        | 2     | Binary      | Indicator variable of whether patient was an inpatient or an outpatient at time of diagnosis                                                                                                                                                                                                  |
| Length of first inpatient stay | 2     | Discrete    | Measured in days, included in model as a binary variable (up to 7 days versus 8 or more days); relevant for inpatients only                                                                                                                                                                   |
| Number of episodes             | 2     | Discrete    | Includes both inpatient admissions and contacts with health services as                                                                                                                                                                                                                       |

|                                                             |       |             |                                                                                                                                                         |
|-------------------------------------------------------------|-------|-------------|---------------------------------------------------------------------------------------------------------------------------------------------------------|
|                                                             |       |             | an outpatient; included in model as a binary variable (up to 7 versus 8 or more)                                                                        |
| Benefit receipt                                             | 3     | Binary      | Comprises both welfare and disability benefit                                                                                                           |
| Deprivation                                                 | 3     | Continuous  | A standardised continuous measure, calculated relative to the general population, and expressed in deciles and included in model as a discrete variable |
| Marital status                                              | 3     | Categorical | Seven categories, converted to binary (unmarried versus all other categories combined)                                                                  |
| Personal income                                             | 3     | Categorical | Calculated relative to the general population, and expressed in deciles and included in model as a discrete variable                                    |
| Children in household                                       | 3     | Binary      | Zero / non-zero                                                                                                                                         |
| Parental psychiatric hospitalisation                        | 3     | Binary      | Use 'care at psychiatric clinic' for this                                                                                                               |
| Parental suicide                                            | 3 (1) | Binary      |                                                                                                                                                         |
| Comorbid depression + schizophrenia                         | - (3) |             | Any prior diagnosis of depression; among patients with a schizophrenia diagnosis only                                                                   |
| Recent death of family member (< 6 months before diagnosis) | 3     | Binary      | Any parent or sibling                                                                                                                                   |

BMI, physical characteristics and IQ were considered as possible Group 2 variables, but subsequently excluded based on the high proportion of missing data

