# Clinical prediction rules for persons diagnosed with an episode of severe mental illness for risk of violent crime and suicide – statistical analysis plan

## Study Summary

**Design:** Retrospective cohort study.

**Data:** Swedish databases linking hospital, crime, prescriptions, family relationships, housing and socio-economic status/deprivation data.

**Participants:** The study cohort is defined as individuals aged 15-65 with a diagnosis of any major psychosis (including bipolar disorder, schizophrenia, schizophrenic spectrum, other psychotic illness), obtained from hospital records that encompass both inpatient and outpatient visits, during the study period.

**Study period:** Psychiatric episodes ('diagnoses') that occurred between 1st January 2001 and 31st December 2008 will be used to develop the model: one episode per person, chosen at random. Data on most risk factors, including prior convictions and family history, are available for the lifespan of the individual, and are therefore not subject to the same 2001 start date for diagnosis. An exception is treatment history, which is available from 2005 onwards.

**Risk factors:** Include demographic characteristics (including gender, age, educational level, birth country), previous offending, drug and alcohol addiction, familial factors (parental and sibling illness, criminality and suicide), treatment history and a measure of deprivation (see Appendix for complete list).

**Primary outcomes:** Two outcomes are specified: (i) any violent crime within 12 months of diagnosis; (ii) suicide within 12 months of diagnosis.

**Outputs:** The main objective is to produce models that estimate the probability of events for the two primary outcomes, with appropriate measures of predictive accuracy.

These models will be used to obtain scoring systems for the calculation of risk to be used prospectively at time of diagnosis. As part of the study, we will investigate whether it is appropriate to assign the resulting probabilities to discrete categories, such as low/medium/high risk.

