## Statistical Analysis

Statistical analysis will be based on logistic regression, adjusting for risk factors, in each of two scenarios:

- (i) Violent crime within 12 months, from time of diagnosis
- (ii) Suicide within 12 months, from time of diagnosis.

Here, 'diagnosis' refers to episodes of psychosis for which a diagnosis was recorded within the period 1st January 2001 to 31st December 2008. The terms 'diagnosis' and 'episode' are used interchangeably in this document.

The method of analysis will be the same in both scenarios, so for clarity the explanation below refers to scenario (i).

In each case, the follow-up period represented in the data-set lasts for at least 12 months after diagnosis, and so it is not necessary to consider the possibility of censoring when performing the analysis.

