### Random selection of diagnoses

Given a starting data-set of all patients and all patient episodes (diagnoses) between 1/1/01 and 31/12/08, patient episodes will be selected at random as follows:

- Select at random, with equal probability, one inpatient or outpatient visit per patient.
- Note that some patients have more than one inpatient or outpatient visit on the same day, and some inpatient or outpatient visits comprise more than one diagnosis; only one inpatient or outpatient visit per day will be considered for random selection (if an inpatient visit and an outpatient visit are listed contemporaneously, the inpatient visit will be used).
- Extraneous episodes that are recorded as occurring within the period of an inpatient stay (because of recording errors or otherwise) will be identified in the data-set as having a date of episode that is earlier than lower-numbered episodes for the same individual; these will also be removed before the random selection step is made.
- If the inpatient or outpatient visit comprises a schizophrenia-spectrum diagnosis (with or without a bipolar diagnosis), this is considered as the diagnosis at time of selection; otherwise bipolar is the diagnosis at time of selection.
- For inpatient stays, the assumed date of diagnosis is the date the inpatient stay ends.
- The randomly selection of diagnoses defines the final data-set for analysis, i.e. there will be no subsequent resampling of diagnoses.

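### The inpatient index date has no alive-at-index condition, so a stay that ends in death can enter a prospective model with no time at risk and an unclear predictor boundary

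*SAP*

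**What the plan says.** **Index date.** SAP, Random selection of diagnoses: "For inpatient stays, the assumed date of diagnosis is the date the inpatient stay ends". No exception is made for stays that end in death.

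**Removals before the draw.** The same section keeps one visit per day and prefers the inpatient record. Of stray episodes inside a stay it says "these will also be removed before the random selection step is made". No listed removal concerns whether the patient was alive at the index date. One visit per patient is then drawn, each with the same chance, and the draw is not repeated.

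**Predictor window.** SAP, Appendix 1, general rule: variables on earlier events "are based on events that happen on or before the date of diagnosis". The row for previous violent crime says instead: "Any violent crime conviction before date of diagnosis". The row "Previous self-harm" is Group 1, so it is always kept in the model, and its notes cell is empty. The general rule therefore applies to it.

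**Outcome window.** SAP, Statistical Analysis: "Suicide within 12 months, from time of diagnosis", with parallel wording for violent crime. Neither this section nor the Study Summary says whether the index day itself counts.

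**Deaths.** SAP, Competing risks: a person who dies before the outcome is coded zero, on the premise that everyone has at least twelve months of follow-up.

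**Use.** SAP, Study Summary: the scores are meant for prospective use when the diagnosis is made.

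**The concern.** A prognostic model needs an index time at which the patient is alive and at risk, predictors known by that time, and outcomes that come after it. The end-of-stay rule breaks the first condition for any stay that ends in death. For an in-hospital suicide, the day-inclusive predictor rule can break the other two as well.

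At stake are the coefficient of a variable that is forced into the suicide model and the accuracy figures for that model. The bootstrap and the geographical validation sample both come from the same data-set, built under the same rules, so neither would expose the problem. Because the draw is made once, a late correction would also cost more. Excluding these stays after the draw would lose patients who had an earlier visit that could have been selected.

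**Working it through.** The SAP gives no figure on this point, so there is none to reproduce. The check is to follow cases through the rules and then to illustrate the size under stated assumptions.

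**Cases under the literal rules**

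1. *Stay ends in a non-suicide death.* The index date is the date of death and time at risk is zero. The competing-risk rule codes both outcomes 0. This does not fit the premise of twelve months of follow-up.
2. *Stay ends in suicide on the ward.* The index date is the date of death. Violent crime is coded 0. Suicide may be coded 1 on day 0, because nothing excludes that day. If the fatal act is recorded as self-harm, the on-or-before rule sets previous self-harm to 1 from the outcome event itself.
3. *Admission after an act of self-harm, death from it days later in the same stay.* The act precedes the index date, so changing the rule to strictly before would not remove it. A condition on the stay is needed too.
4. *Violent crime on the index day.* The row note requires a conviction before that day, so the direct path is closed. What remains is the contradiction with the general rule.

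**Size for previous self-harm in the suicide model**

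Assumed inputs (none is in the SAP):
- p0 = 0.20, prevalence of prior self-harm in non-cases, so odds 0.20/0.80 = 0.25
- true odds ratio 3.0, so odds in cases 0.75 and p1 = 0.75/1.75 = 0.4286
- f = share of counted suicides that are day-0 cases
- q = share of those coded as previous self-harm

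Formulas: apparent prevalence in cases pa = (1 − f) × p1 + f × q; apparent odds ratio = [pa/(1 − pa)]/0.25.

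| f | pa, q = 0 | OR, q = 0 | pa, q = 1 | OR, q = 1 |
|---|---|---|---|---|
| 2% | 0.4200 | 2.90 | 0.4400 | 3.14 |
| 5% | 0.4071 | 2.75 | 0.4571 | 3.37 |
| 10% | 0.3857 | 2.51 | 0.4857 | 3.78 |

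For example, with f = 10% and q = 1: pa = 0.9 × 0.4286 + 0.1 = 0.4857, odds 0.4857/0.5143 = 0.944, and 0.944/0.25 = 3.78.

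The sign changes where q = p1, that is at about 43%. Below that share of day-0 suicides coded as self-harm, the estimate falls; above it, the estimate rises.

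**Sensitivity to the inputs.** With p0 of 15% to 30%, f = 10% and q from 50% to 100%, a true odds ratio of 2.0 appears as 2.03 to 2.85, and one of 3.0 as 2.92 to 3.96. With f = 2% the ranges are 2.01 to 2.16 and 2.98 to 3.18.

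**The case against.** The strongest reply is that this rests on silence. No sentence says that stays ending in death are kept, and an alive-at-index condition could stand in a protocol that is not shown. Against that, this SAP itself fixes the index date, the eligible visits and the removals before the draw. An analyst who follows it as written would keep these stays. The rule as stated gives the wrong result; the point is more than missing detail.

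A second reply is that on-or-before is reasonable in itself, because what is recorded by discharge is known when a living patient is scored. This stands. The wording harms only when the recorded act is the outcome event, and it still has to be reconciled with the violent-crime row.

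A third reply is that coding a competing death as zero is a coherent definition of twelve-month absolute risk. This also stands for deaths after the index date. It does not justify including patients who were never at risk.

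Several stronger readings are tempting, and the SAP does not support them:
- *That day 0 is outcome time by rule.* The first outcome day is left unstated.
- *That violent crime leaks into its own predictor.* The row note prevents the direct path.
- *That the self-harm odds ratio and the model's accuracy are necessarily inflated.* The odds ratio can move either way, depending on how fatal acts are coded.
- *That the inpatient coefficient is inflated.* Hospital deaths coded zero pull it down while in-hospital suicides pull it up, and the net effect is unknown.
- *That the draw favours a dead patient's last visit.* Each of a patient's eligible visits has the same chance.

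**Conclusion.** The point holds in a limited form. The end-of-stay index date, without a condition that the patient is alive, admits patients with no time at risk to a model meant for prospective scoring. In the suicide model it also opens a path by which the fatal act can count as a forced-in predictor. Separately, Appendix 1 contradicts itself on whether the index day is predictor time.

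The size is unknown, because the SAP gives neither the number of stays that end in death nor the way fatal acts are coded. Under the assumptions above the effect is small if day-0 suicides are about 2% of cases. It is material only if they make up several percent and are coded mostly one way. The change should be made because the rule is wrong for the stated use and cheap to correct; a large bias has not been shown.

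**What to change.** 1. In Random selection of diagnoses, remove stays that end in death from the eligible visits **before** the random draw. A patient with an earlier eligible visit can then still be selected, and a later in-hospital suicide within twelve months of that visit remains a valid outcome.
2. In Appendix 1, use one predictor boundary throughout, so that the general rule and the violent-crime row agree.
3. State that an act which is itself the outcome event, or which led to it, is never counted as a predictor.
4. State how the index day is treated for outcomes. Starting every outcome on the following day is not needed and would discard genuine events after discharge on the same day. These can be kept where the order of events is known.

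The cost is a few sentences, one data step and the loss of a few events. It would help to report how many stays are removed, by cause of death, so that a reader can judge the size.

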## Appendix 2: Classification of regions for selection of external validation sample

| Group 1                | Group 2                                   | Group 3                        | Group 4                         |
|------------------------|-------------------------------------------|--------------------------------|---------------------------------|
| Major urban centres    | Counties with major urban centres removed | Counties with small population | Counties with medium population |
| 1 Stockholm City North | 1 Stockholm County Other                  | 7 Kronoberg                    | 3 Uppsala                       |
| 1 Stockholm City South |                                           | 9 Gotland                      | 4 Södermanland                  |
| 12 Malmö               | 12 Skåne Other                            | 10 Blekinge                    | 5 Östergötland                  |
| 14 Gothenburg          | 14 Västra Götaland Other                  | 23 Jämtland                    | 6 Jönköping                     |
|                        |                                           |                                | 8 Kalmar                        |
|                        |                                           |                                | 13 Halland                      |
|                        |                                           |                                | 17 Värmland                     |
|                        |                                           |                                | 18 Örebro                       |
|                        |                                           |                                | 19 Västmanland                  |
|                        |                                           |                                | 20 Dalarna                      |
|                        |                                           |                                | 21 Gävleborg                    |
|                        |                                           |                                | 22 Västernorrland               |
|                        |                                           |                                | 24 Västerbotten                 |
|                        |                                           |                                | 25 Norrbotten                   |

Regions will be selected at random, with equal probability, as follows:

- One region from Group 1
- One region from Group 2 (under the constraint that no more than one region in Groups 1 and 2 from the same county can be selected)
- One region from Group 3
- Sequentially select from Group 4 until the number of violent crime events in the sample reaches at least 180
